## Abstract

**Background::**

Diabetic retinopathy is not only the most common complication of diabetes, but also 1 of the main causes of blindness, which seriously affects the physical and mental health of patients. Panretinal photocoagulation is a common method for the treatment of diabetic retinopathy, but it has some defects. Qiming granule has advantages in the treatment of diabetic retinopathy, but there is a lack of standard clinical research to verify it. Therefore, the purpose of this randomized controlled trial is to evaluate the efficacy and safety of qiming granule combined with laser in the treatment of diabetic retinopathy.

**Methods::**

This is a prospective randomized controlled trial to study the efficacy and safety of Qiming granule combined with laser in the treatment of diabetic retinopathy. Approved by the Clinical Research Society of our hospital. The patients are randomly divided into a treatment group (Qiming granule combined with laser treatment group) or control group (simple laser treatment group). The patients are followed up for 12 months after 6 months of treatment. Observation indexes include total effective rate, corrected visual acuity, macular fovea thickness, adverse reactions and so on. Data are analyzed using the statistical software package SPSS version 18.0 (Chicago, IL).

**Discussion::**

This study will evaluate the clinical efficacy and safety of qiming granule combined with laser in the treatment of diabetic retinopathy. The experimental results of this study will provide a reliable reference basis for clinical use of qiming granule combined with laser in the treatment of diabetic retinopathy.

**Trial registration::**

OSF Registration number: DOI 10.17605/OSF.IO/ZEQPB.

## Introduction

1

With the change of diet, the aging of the population and the influence of the environment, the prevalence rate of diabetes has increased significantly. According to the statistics of the International Diabetes Federation, there are about 415 million people with diabetes in the world. It is estimated that the number of people with diabetes will reach 642 million by 2040.^[1]^ Diabetic retinopathy (DR) is a diabetic microvascular complication. As 1 of the main diseases causing blindness, diabetic retinopathy has become the main cause of visual disability and blindness in young adults.^[2]^ About 1/3 of diabetics will develop symptoms of diabetic retinopathy, and 1/3 of them will definitely have severe retinopathy or macular edema.^[3]^ In addition to the impact on vision, the existence of diabetic retinopathy also means an increased risk of systemic vascular complications, constantly endangering the lives of patients.^[2]^

Panretinal Photocoagulation (PRP) is a common method to treat and control the progression of DR.^[4,5]^ However, in addition to the therapeutic effect, PRP can also increase the temperature of local tissue of the eye, resulting in thermal degeneration of local tissue, destruction of blood-retinal barrier, macular edema.^[6]^ Damage to retinal ganglion cell axons, resulting in a continuous decrease of peri-optic disc nerve fibers, and complications such as vision loss and visual field defect caused by photocoagulation injury.^[7]^

Traditional Chinese medicine is an effective treatment of Chinese traditional medicine, which is widely used in the clinic. Qiming granule is a compound preparation of traditional Chinese medicine, which can improve the function of retinal microcirculation, reduce vascular permeability, reduce microvascular leakage and promote the absorption of macular edeman.^[8]^ There is evidence that qiming granule combined with PRP can reduce the expression of serum inflammatory factors, inhibit neovascularization, and help to improve the clinical efficacy of patients with DR.^[9]^ However, there is no clinical study on the efficacy and safety of qiming granule combined with PRP in the treatment of diabetic retinopathy. Therefore, we intend to use this randomized controlled trial (RCT) to evaluate the efficacy and safety of qiming granule combined with PRP in the treatment of diabetic retinopathy.

## Materials and methods

2

### Study design

2.1

This is a prospective RCT to study the clinical efficacy and safety of qiming granule combined with laser in the treatment of diabetic retinopathy. This study will follow the comprehensive trial reporting standard.^[10]^ The flow chart is shown in Figure 1.

**Figure 1 F1:**
[figure not shown]
Flow diagram.

### Ethics and registration

2.2

This research scheme is in line with the Helsinki Declaration and has been reviewed by the Clinical Research Ethics Committee of our hospital. This protocol is registered at OSF (registration number: DOI 10.17605/OSF.IO/ZEQPB). Before being randomly divided into groups, all patients are required to sign an informed consent form, and they can choose whether or not to continue the trial at any time.

### Sample size

2.3

The calculation of sample size is based on the mean and standard deviation of best corrected visual aculty (BCVA) at 3 months after surgery. According to the results of the pilot study, the experimental group is 0.37 ± 0. 14, and the control group is 0.44 ± 0.13. Set α = 0.025, 1 sided test, β = 0.20. Calculated by the PASS15.0 software, each group needs 60 participants, with an estimated withdrawal rate of 10%, and each group will include 67 participants.

### Patients

2.4

Inclusion criteria:① Diagnostic criteria and staging standards of DR: Adopted international disease severity scale for DR proposed by the Global Diabetic Retinopathy Project Group in 2002.^[11]^ The diagnosis is confirmed by fundus fluorescein angiography, and retinopathy stage II to IV; ② age range18 to 70 years; ③ blood glucose control 5–7.8 mmol / L; ④ signed informed consent.

Exclusion criteria: ① significantly impaired liver function, defined as ALT above 1.5 times upper limit of the normal level; ② patients who underwent other clinical trials in the last 3 months; ③ patients with poor glycemic control; ④ with severe primary diseases, such as cardiovascular, liver or kidney disease or mental illness; ⑤ accompanied by other ocular complications, such as glaucoma, severe cataracts, poor vision, retinal detachment, ophthalmic nerve disease, uveitis and retinopathy not related to DM.

### Study design

2.5

Eligible participants are randomly assigned to either the treatment group or the control group in a 1:1 ratio using a random tool based on a central network. The random sequence randomization is performed without any stratification by independent statisticians who do not participate in the implementation of the experiment or statistical analysis using SAS 9.3 software (SAS Institute, Cary, NC). The clinical research coordinator enters participant information on the tablet and is given a random number. The research assistant gets the allocation of participants from the computer. Throughout the study, the research assistant is responsible for screening, recruiting participants, and assigning random numbers to participants who have been included. Results the evaluator is responsible for the evaluation of the scale. Considering the actual operational nature of acupuncture, participants and practitioners may be aware of random distribution. However, the evaluators of research results and the statisticians of data statistics and analysis are not informed of the distribution situation.

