### Statistical analysis

2.9

The collected data are analyzed by SPSS 18.0 software. A chi-square test is used for counting data, mean ± standard deviation ($\bar{x}\pm s$) is used for measurement data, independent sample *t* test is used for normal distribution. Mann-Whitney *U* test is used for skewed distribution. When *P* *<* .05, and the difference is considered to be statistically significant.

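### Randomisation is unstratified and the stated tests are crude although retinopathy stage is known at entry; the plan stays valid but gives up inexpensive precision and baseline balance

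*Protocol article*

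**What the plan says.** On allocation, section 2.5 says that participants are "randomly assigned to either the treatment group or the control group in a 1:1 ratio" through a central network tool, and that "The random sequence randomization is performed without any stratification by independent statisticians". Stratification is therefore ruled out in so many words; it is not merely unmentioned.

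On entry, section 2.4 requires that "The diagnosis is confirmed by fundus fluorescein angiography, and retinopathy stage II to IV". Stage is thus on record for every patient before randomisation.

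On size, section 2.3 uses 3-month BCVA: "the experimental group is 0.37 ± 0. 14, and the control group is 0.44 ± 0.13". The error rates are "Set α = 0.025, 1 sided test, β = 0.20", and the result is that "each group needs 60 participants, with an estimated withdrawal rate of 10%, and each group will include 67 participants".

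On analysis, section 2.9 says "A chi-square test is used for counting data" and gives a two-sample t test or a Mann-Whitney U test for measurements. It mentions no term or stratum for stage.

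**The concern.** Stage is a severity grade, so it plausibly relates to the efficacy outcomes in section 2.7: acuity, macular thickness, and a total effective rate built from lesions, acuity lines and visual field. In a single-centre trial of 134 patients, one arm can by chance receive more advanced disease. As written, neither the allocation nor the stated tests take account of that.

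Two things are at stake. Variation in outcome due to stage stays in the standard error although it could be removed. And a visible difference in stage at baseline would make the result harder to defend, whichever way it falls. A baseline-BCVA covariate would not settle this for the categorical outcome, which is compared by a plain chi-square test.

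**Working it through.** **1. The plan's own sample size.** Inputs from section 2.3: difference 0.44 − 0.37 = 0.07; SD = √((0.14² + 0.13²)/2) = 0.1351; one-sided α 0.025; power 80%.

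- Normal approximation: n = 2 × (0.1351 × (1.960 + 0.842)/0.07)² = 58.5, so 59 per group.
- Noncentral t: power is 79.7% at 59 and 80.4% at 60, so 60 per group.
- Withdrawal: 60/0.90 = 66.7, so 67 per group.

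The stated 60 and 67 are reproduced.

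**2. How often stage is visibly unbalanced.** Assumption: stages II, III and IV are equally common; the article does not give the mix. With 67 per arm, the SD of the between-arm difference in one stage's share is √((1/3)(2/3)(2/67)) = 8.1 percentage points. By simulation:

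- a given stage differs by at least 10 points (7 patients) in about 23% of randomisations;
- at least one of the three does so in about 46%;
- at least one differs by 15 points or more in about 13%.

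**3. What such an imbalance does to the BCVA comparison.** Let R² be the share of BCVA variance explained by stage. The article does not give it, so a range is assumed. The 1-SD shift is √R² × 0.1351 × √(2/67). At R² = 10% this is 0.316 × 0.1351 × 0.1728 = 0.0074 logMAR, and 0.0074/0.07 = 10.5%.

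**4. What adjusting for stage gains.** With allocation balanced on stage and stage in the model, the residual SD is 0.1351 × √(1 − R²). At R² = 10% and 60 per group the standard error is 0.0234, and power is Φ(0.07/0.0234 − 1.96) = 84.9%.

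| Assumed R² | 1-SD shift (share of 0.07) | 95% limit (share of 0.07) | Chance shift exceeds a quarter of 0.07 | Power, stratified and adjusted: normal approx. / t test |
|---|---|---|---|---|
| 2% | 0.0033 (5%) | 0.0065 (9%) | <0.1% | 81.8% / 81.2% |
| 5% | 0.0052 (7%) | 0.0102 (15%) | <0.1% | 82.9% / 82.3% |
| 10% | 0.0074 (11%) | 0.0145 (21%) | 1.8% | 84.9% / 84.3% |
| 20% | 0.0104 (15%) | 0.0205 (29%) | 9.4% | 88.7% / 88.2% |

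Without adjustment, power at 60 per group is 81.0% by normal approximation (Φ(0.07/0.0247 − 1.96)) and 80.4% by t test.

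**5. Whether the plan as written is valid, and where the gain comes from.** Trials were simulated with 60 per group, three equally frequent stages, unstratified allocation and 20,000 trials per setting.

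- The unadjusted t test kept one-sided type I error at 2.4% to 2.7% and power at 80% to 81% for R² from 0 to 30%.
- Adding a stage term, still with unstratified allocation, gave power of 81.7%, 84.2% and 88.2% at R² of 5%, 10% and 20%.

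Set against the t-test column above (82.3%, 84.3%, 88.2%), stratifying the list adds less than one point of power. Its further benefit is balance at baseline.

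**The case against.** The strongest reply is that unstratified 1:1 randomisation is an accepted and valid design for a single-centre trial of this size. Chance imbalance in stage is ordinary sampling variation and is already inside the SDs of 0.14 and 0.13 used for sizing. That stands, and step 5 confirms it. An analysis plan that is not shown may also add a stage term, so nobody can say from this article that stage will never be accounted for. It could not, however, undo the allocation that section 2.5 fixes.

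A reader might go further and infer three things that the article does not support:

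- *That the design inflates false claims for the granule.* Over randomisations it does not. Only conditional on an adverse realised imbalance does the chance move. For a shift of 0.015 logMAR in the granule's favour at 60 per group, it is Φ(−(1.96 × 0.0247 − 0.015)/(0.0247 × √(1 − R²))). That gives 4.5% if BCVA worsens by an assumed 0.10 logMAR per stage (R² 37%) and 7.8% at 0.05 per stage (R² 9%), where a shift that large is a 2-SD event. Imbalances the other way offset these.
- *That the design cannot deliver 67 per group.* Section 2.5 excludes stratification, not blocking. An unstratified blocked list gives equal groups.
- *That imbalance would typically move the result by a large part of 0.07.* This needs a strong association between stage and BCVA, and the article reports none.

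**Conclusion.** The point holds as a modest improvement in precision and credibility. It is not a flaw in validity. Section 2.5 makes an explicit choice not to balance on a severity grade that the trial already records, and section 2.9 states only tests that ignore it.

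The size rests on two assumptions: equal thirds for the chance of imbalance, and R² of 2% to 20% for its effect. On these, the typical shift is about 5% to 15% of the target difference, and the power available at 60 per group is roughly 82% to 89% (about half a point lower by t test) against about 80% now. Most of that comes from the stage-adjusted analysis, and it shrinks to the extent that baseline BCVA, if adjusted for, already carries stage. The gain is still worth having because the trial is sized with almost no reserve (80.4% at 60 per group).

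**What to change.** In section 2.9, include DR stage (II, III, IV) as a term in the BCVA and macular thickness comparisons, and compare the total effective rate by a Cochran-Mantel-Haenszel test stratified by stage.

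In section 2.5, if enrolment has not started, stratify the central list by DR stage, using permuted blocks of randomly varying size that are not disclosed to site staff. Concealing the block sizes matters because the article accepts that participants and practitioners may know the allocation. If enrolment has started, keep the existing sequence and make only the analysis change.

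The cost is a reconfigured list in a tool already in use and a short addition to the analysis section. Stage must be entered before allocation, and with three strata a few blocks will stay incomplete. No patients or visits are added.

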### Intervention measures

2.6

All patients are given oral western medicine routine hypoglycemic drugs, and the medication is recorded.

In the control group, the laser treatment is carried out by the unified treatment team. After the compound tropicamide fully dilated pupil, obucaine hydrochloride eye drops are anesthetized. PRP is treated with 532 fundus laser therapeutic apparatus (Lumenis, Novus Spectra). Macular grid photocoagulation is performed first (spot diameter 100 μm, function 80–100mW, exposure time 0.1 s), followed by panretinal photocoagulation (posterior polar spot diameter 200 μm, peripheral spot diameter 300 to 500 μm, exposure time 0.15 to 0.20 s, total photocoagulation 1200–1600), 3 to 4 times to complete. The interval is 1 week at a time. Fundus fluorescein angiography is reexamined for 3 months to decide whether to supplement photocoagulation therapy.

On the basis of the control group, the observation group is given qiming granule (Zhejiang Wansheng, Chinese medicine Z20090036, Specification 4.5 g/ bags), taken with warm water, 1 bag per time, 3 times a day. The medicine is taken continuously for 6 months.

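### The masking section lets practitioners know the allocation for a reason that does not apply here (acupuncture), so laser given after randomisation within wide ranges could differ by arm before the 3-month visual acuity visit

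*Protocol article*

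**What the plan says.** **Masking (Section 2.5).** With acupuncture given as the reason, the article states that "participants and practitioners may be aware of random distribution". It then adds that "the evaluators of research results and the statisticians of data statistics and analysis are not informed of the distribution situation". The only person named as obtaining the allocation is the research assistant. The limitations paragraph that closes the Discussion concedes that strict double-blinding is not achievable.

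**Laser (Section 2.6).** In the control-group paragraph, "the laser treatment is carried out by the unified treatment team". Panretinal laser is specified by "posterior polar spot diameter 200 μm, peripheral spot diameter 300 to 500 μm" and "exposure time 0.15 to 0.20 s, total photocoagulation 1200–1600", over 3 to 4 sessions a week apart. The treatment arm has the same laser plus the granule: "On the basis of the control group, the observation group is given qiming granule".

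**Effects of laser (Introduction and Discussion).** The Introduction says that "PRP can also increase the temperature of local tissue of the eye" and goes on to list macular oedema, loss of vision and visual field defects as consequences. The Discussion repeats this.

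**Outcomes and sizing (Sections 2.3 and 2.7).** Best corrected visual acuity (BCVA) and central macular thickness are outcomes, and visual field enters the total effective rate. The sample size rests on BCVA at 3 months.

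**The concern.** The comparison isolates the granule only if the laser is the same in both arms on average. Three features together put that at risk.

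- The laser comes after randomisation.
- It is specified as ranges.
- The masking rule allows practitioners to know the arm, for a reason taken from a different kind of trial.

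An operator who knows that one patient has an added treatment and another does not could, even unintentionally, treat the two differently while staying within the protocol. By the protocol's own account, laser acts on the same quantities that the trial measures. Masked assessors would then measure, quite accurately, a difference that came partly from the laser. This concerns the initial laser course, not the supplementary laser considered at 3 months.

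**Working it through.** **1. Does the stated reason fit?** Section 2.6 describes laser in one arm, and laser plus an oral granule in the other. Neither includes acupuncture. A granule taken by mouth does not disclose the arm to a laser operator through the procedure itself. The reason given in Section 2.5 therefore does not apply to the laser team.

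**2. Timing.** Three to four sessions one week apart span 2 to 3 weeks from first to last. The initial course is over before the 3-month BCVA.

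**3. Width of the ranges.** Nominal area = burns × π × (diameter/2)². Counts and diameters are from Section 2.6.

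- If every burn were peripheral: 1200 × π × 0.15² = 84.8 mm² and 1600 × π × 0.25² = 314.2 mm², a ratio of 3.70.
- The same sentence sets posterior burns at 200 μm, and the posterior share is not given. With an assumed common share at both extremes:

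| Posterior share (assumed) | Lowest, mm² | Highest, mm² | Ratio |
|---|---|---|---|
| 0% | 84.8 | 314.2 | 3.70 |
| 10% | 80.1 | 287.8 | 3.59 |
| 25% | 73.0 | 248.2 | 3.40 |
| 50% | 61.3 | 182.2 | 2.97 |
| 75% | 49.5 | 116.2 | 2.35 |

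For shares from 0% to 50% the range is about 3 to 3.7-fold. It compares the lowest and highest permitted patient, not two arm means.

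**4. The plan's own sample size.** Inputs from Section 2.3: means 0.37 and 0.44, SDs 0.14 and 0.13, one-sided α 0.025, power 0.80.

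- Pooled SD = √[(0.14² + 0.13²)/2] = 0.135; difference = 0.07.
- n = 2 × (1.960 + 0.842)² × 0.135² / 0.07² gives 59 per group by the normal formula and 60 by the t version. Then 60/0.90 = 66.7, so 67. The stated figures reproduce.

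**5. Illustration of what a laser-driven shift would do.** The documents give no link between burn area and logMAR, so the shift of 0.02 is assumed. It is 0.02/0.07 = 29% of the planned effect.

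- Standard error at 60 per group = 0.1351 × √(2/60) = 0.0247.
- Shift towards the granule, with no true effect: 1 − Φ(1.960 − 0.02/0.0247) = 1 − Φ(1.149) = 12.5%, or 12.4% by the t-test, against the nominal 2.5%.
- Shift against the granule, with the planned effect true: the apparent difference is 0.07 − 0.02 = 0.05, and power is Φ(0.05/0.0247 − 1.960) = Φ(0.067), about 53%, against 81% without the shift by the same approximation.

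**The case against.** The strongest reply has five parts.

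- **One regimen, one team.** Laser is defined identically for both arms and given by a unified team. This stands as far as it goes: it limits variation between operators. It does not keep that team unaware of the arm.
- **Ranges are ordinary.** Stages II to IV are admitted, so patients will need different amounts of laser, and randomisation balances severity on average. This also stands. The ranges are not a defect in themselves; they matter because operators may know the arm.
- **Detail belongs in the full protocol.** A selection rule and a treatment record may well be there, and their absence from an article is no finding alone. The reason given for not masking practitioners, however, is stated in the article and does not fit the trial.
- **The limitation is already admitted.** The Discussion acknowledges imperfect blinding, but acknowledging it does not show that the laser team has to know the arm.
- **The bias is only possible.** This stands in full. Section 2.5 says that unspecified practitioners may be aware, not that laser operators are.

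A reader might infer more than the documents support. An almost fourfold range would need every burn to be peripheral, although posterior burns are part of the regimen. Operator discretion is an inference from the absence of a stated rule. Bias in favour of the granule is not established either: an operator who trusts the granule to protect the macula might give that arm more laser, which could work against it.

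**Conclusion.** The point holds as a weakness in a stated masking rule, not as evidence that the arms will receive different laser. The reason for leaving practitioners unmasked is wrong for this trial, and nothing described requires the laser operator to know the allocation. Within the stated ranges, nominal burn area can differ between patients by up to about 3 to 3.7-fold, if the posterior share is the same at both extremes and no more than half of the burns. Any difference between arm means would be smaller and cannot be derived from the documents. The figures of about 12% error or about 53% power rest wholly on an assumed 0.02 logMAR shift and show sensitivity only. Because laser precedes the 3-month BCVA and acts on the outcomes themselves, masked assessment does not protect against this route. The sample size of 60, inflated to 67, is unaffected.

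**What to change.** In Section 2.5, delete the acupuncture rationale and state that:

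- the laser team is not told the allocation;
- the research assistant who obtains it arranges granule supply separately;
- patients are asked not to mention their medicine at laser sessions.

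In Section 2.6, add that delivered laser (burns, spot size, power, exposure time, number of sessions) is recorded for each patient and reported by arm, so that any imbalance can be seen.

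Laser settings do not change. I would not ask for the whole laser plan to be fixed before allocation is opened, because that could constrain adjustment between sessions.

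The cost is protocol wording and one record form, with no extra staff or procedure. The downside is that masking will be partial, since some patients may reveal their arm; the table of delivered laser by arm then shows whether the laser differed.
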